## Introduction

 Childhood stroke has a pooled incidence of 2.1 per 100 000 person-years.^1^ Global impact is growing, with a 35% increase in prevalence from 1990 to 2013.^2^ Childhood stroke is associated with high rates of neurological impairment and substantial economic costs.^3
4^ Stroke is eminently treatable but time-critical. Reperfusion therapies, which include intravenous thrombolysis and endovascular clot retrieval (ECR), are established as effective to improve long-term outcomes of adults with acute ischaemic stroke.^5
6^

The catchcry in emergency stroke treatment that *time is brain* is equally applicable to children because failure to save brain results in poorer outcomes.^7^ Survivors of childhood stroke face decades of living with disability and with that comes a significant impact on their families and the broader community. The long-term economic and societal cost of childhood stroke is not well elucidated, with previous US studies reporting the economic impact only up to 5 years from stroke event.^3^

The days of therapeutic nihilism in adult stroke have passed, yet children are still not receiving the benefits of reperfusion therapies, often because of diagnostic delay, sometimes extending beyond 24 hours.^8^ Delays prior to arrival relate to limited awareness of stroke among caregivers,^9^ clinical recognition among paramedics^10^ and emergency physicians,^11^ and poor accuracy and reliability of prehospital decision support tools.^12^ In contrast to adults, in-hospital factors—particularly delayed access to rapid diagnostic imaging in the emergency department (ED)^13^ and poor sensitivity of CT-based imaging for detection of infarction in children with arterial ischaemic stroke (AIS)^14^—are more important contributors to delayed diagnosis than prehospital factors. Therefore, institutional and regional systems of acute care are required to streamline diagnosis and initial treatment of childhood stroke.

In adults with stroke, there has been a move towards tissue-based rather than time-based selection of candidates for reperfusion therapies to salvage viable brain. This approach using advanced brain imaging, which quantifies penumbral tissue destined for infarction if blood-flow is not restored, has led to use of thrombolysis^15
16^ and ECR^17^ in extended time windows beyond 4.5 and 6 hours, respectively. These diagnostic advances have only recently been tested in observational studies in children^18

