### Interventions

#### Code Stroke protocol development and implementation (all PACS sites)

A Code Stroke protocol^35
36^ is a hospital-based protocol and multidisciplinary emergency response system designed to standardise initial clinical assessment and urgent imaging of children with suspected stroke, informed by evidence-based guidelines.^28
29^ Components along the process of care, which begins on arrival in the ED, include recognition of symptoms associated with stroke^37^ at the time of triage, which leads to activation of Code. This triggers rapid clinical assessment by ED physicians. Neurologists will confirm the presence of neurological signs and assess the severity of symptoms using the paediatric adaptation of the National Institutes of Stroke Severity Scale (pedNIHSS),^38^ and in the context of ischaemic stroke, to screen children for eligibility and contraindications to reperfusion therapies, which includes collection of bloodwork. The clinicians decide the need for and type of brain imaging (CT or MRI) to confirm stroke diagnosis. Imaging leads to decisions about reperfusion therapies for ischaemic stroke or neurosurgical intervention for HS. An example of a Code Stroke pathway is presented in figure 1.

The five tertiary paediatric hospitals without established institutional Code Stroke protocols at commencement of the study will develop and implement the protocols through establishment of multidisciplinary working groups including—but not limited to—paediatric ED physicians, neurologists, neurosurgeons, radiologists, stroke research nurses, anaesthetists, intensivists, haematologists and neuro-interventional radiologists. Current practice will be evaluated through engagement of these stakeholders, and site-specific analysis of barriers and enablers to improving stroke diagnosis will be identified, drawing on previous conceptual modelling using Value Focused Process Engineering to map the process of care in children with suspected stroke.^39^

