## Data collection

### Pre-implementation and pre-protocol development phase

All sites will retrospectively collect data for confirmed strokes by case record review from 2015 to 2017, using the ICD-10 codes: I61.0–I61.6, I61.8, I61.9, I62.9, I63.0–I63.6, I63.8, I63.9, I64.0 and G45, for the primary aim of determining time to diagnosis prior to implementation of Code Stroke protocols across study sites (table 1).^40
41^

**Table 1 T1:** Data to be collected

Variables	Pre-implementation (2015–2017) confirmed stroke	Post implementation phase (2018 onwards) stroke	Post implementation phase (2018 onwards) mimics
Demographics	✓	✓	✓
Prehospital care*	✓	✓	✓
Presenting clinical features	✓	✓	✓
pedNIHSS (baseline, 24 and 48 hours)	✓†	✓	✓‡
EMS call taker and paramedic coded diagnoses*	✓	✓	✓
Sensitivity of ED physician diagnosis		✓	✓
Time to diagnosis§	✓	✓	✓
Timelines of care (pre- and post-arrival)	✓	✓	✓
Length of stay, acute hospital and inpatient rehabilitation	✓	✓	✓¶
Follow-up phone call following ED discharge for mimics to confirm no change in diagnosis		✓	✓
Rates of reperfusion therapy use (t-PA and ECR)	✓	✓	
Reperfusion therapy related serious adverse events	✓	✓	
Neurological outcomes: Outcomes: (PSOM and mRS) at discharge 7, 30 and 90 days. mRS at 30 and 90 days	✓	✓	
Child Health Utility (CHU-9D)		✓	
Costs of childhood stroke, using hospital/Medicare linked services health utilisation cost data		✓	

* For the subgroups of children transported to ED by ambulance.

† Paediatric version National Institutes of Health Stroke Scale (pedNIHSS) and Paediatric Stroke Outcome Measures (PSOM) may be derived retrospectively in some (but not all) patients from clinical assessment notes and should be collected if applicable.

‡ Only at baseline.

§ Time to diagnosis will be collected for all children presenting to the emergency department, regardless of mode of arrival and for inpatients where a Code Stroke is activated.

¶ Only if admitted.

ECR, endovascular clot retrieval; ED, emergency department; EMS, emergency medical services; mRS, modified Rankin score; tPA, tissue plasminogen activator.

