## Sample size and power calculations

We anticipate 326 patients with suspected stroke will be recruited during the protocol development and prospective phases of the study (based on numbers of patients recruited to institutional stroke registries in Victoria and New South Wales). Recent literature suggests that approximately one in three children with stroke symptoms will have a final diagnosis of stroke following imaging.^31
43–45^ Therefore, we anticipate 98 participants with a radiologically confirmed diagnosis of stroke in each study phase. Estimates of pre-implementation time to stroke diagnosis are based on extrapolation of local published data^13^ and audit data provided by three study sites. Estimates of post implementation time to stroke diagnosis are based on audit data from Queensland Children’s Hospital, where the proportion of children diagnosed within 4.5 hours increased from 15% to 40% during the 12-month period following introduction of their institutional PACS in 2019. We estimate that 15% of children will be diagnosed within 4.5 hours in the pre-implementation phase, increasing to 40% in the post implementation phase.

The *primary outcome* is the change in the proportion of children with stroke diagnosed within a 4.5-hour time window for reperfusion therapies, pre- and post-PACS implementation (figure 4). Time to diagnosis will be based on radiological confirmation of ischaemic infarction or haemorrhage on CT or MRI. This will be determined by calculating the time elapsed from last seen well to completion of neuroimaging, which is electronically recorded on imaging studies.

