## Data analysis plan

### Outcomes

The *primary outcome* is the change in the proportion of children with stroke diagnosed within a 4.5-hour time window for reperfusion therapies, pre- and post-PACS implementation. This will be estimated using a mixed-effect logistic regression model with the dichotomous variable ‘diagnosed within 4.5-hour time window (yes/no)’ as the dependent variable, implementation phase as an independent fixed effect and hospitals as random effects.

*Secondary outcomes* (figure 4) include:

The proportion of children receiving reperfusion therapies will be analysed as for the primary outcome.Accuracy of emergency medical services (EMS) call taker, paramedic and ED physician stroke diagnosis against the gold standard diagnosis of radiologically confirmed stroke. Change in correctness of stroke (vs mimic) diagnosis, pre-implementation and post implementation of PACS will be estimated using a random-effect logistic regression model with dichotomised correctness of diagnosis as the dependent variable, intervention phase as an independent variable and hospital as a random effect.The impact of EMS call taker, paramedic and ED physician actions (eg, lights/sirens response and prenotification, PACS activation, MRI selection as the first imaging study in suspected AIS) on time to diagnosis will be analysed. Differences in times will be analysed using clustered quartile regression, with hospitals as clusters.The economic impact of shorter time to diagnosis, increased utilisation of MRI imaging and increased rates of reperfusion therapy in stroke patients will be measured using the CHU-9D, and hospitals linked services health utilisation and cost data.

Markov cohort model will be developed to quantify per-capita, national healthcare and societal costs economic costs, and the associated lifetime loss of QALYs and life years.

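### The secondary analysis of EMS and ED actions times diagnosis from last seen well, so its outcome includes delay that the actions could not have changed

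*Protocol article*

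**What the plan says.** The Sample size section defines time to diagnosis once: "This will be determined by calculating the time elapsed from last seen well to completion of neuroimaging". The Data analysis plan (Outcomes) then uses the same term, with no other start point, for a secondary analysis of what EMS and ED staff do. Its examples are the lights/sirens response, prenotification, activation of the Paediatric Acute Code Stroke (PACS) protocol and MRI as the first study; the sentence ends "PACS activation, MRI selection as the first imaging study in suspected AIS) on time to diagnosis will be analysed". The method is stated as follows: "Differences in times will be analysed using clustered quartile regression, with hospitals as clusters". No covariate is named.

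Three other places bear on the point.
- The Interventions section places the Code Stroke process after arrival: "Components along the process of care, which begins on arrival in the ED".
- Table 1 lists timelines both before and after arrival, for the pre-implementation strokes and for post-implementation strokes and mimics.
- The Introduction says that in children the in-hospital factors "are more important contributors to delayed diagnosis than prehospital factors".

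**The concern.** This analysis compares children who had an action with children who did not. It is separate from the comparison of phases. PACS activation and the choice of first imaging can change only what follows ED arrival. Prenotification and a lights/sirens response can change only what follows the emergency call. The defined clock starts earlier than either.

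Two consequences follow. First, variation in the earlier delay enters the outcome as noise and reduces precision. Second, if children who present early are more or less likely to receive the action, the difference in earlier delay appears as an effect of the action. The Discussion expects the study's work on decision support to inform paramedic guidelines. A misleading account of which actions shorten diagnosis would therefore matter, although it would leave the primary outcome untouched.

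**Working it through.** **What the article gives.** It states no power, effect size or time distribution for this analysis, so there is no figure to reproduce. Its one power statement (80% for 15% versus 40%) concerns the primary outcome and does not carry over.

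**Decomposition.** Write T = D + H, where D is the delay before the action is possible and H is the time after. For action A, in means:

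E[T | A=1] − E[T | A=0] = (E[D | A=1] − E[D | A=0]) + (E[H | A=1] − E[H | A=0])

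The first bracket cannot be an effect of A. If A is unrelated to D, that bracket is zero but the spread of D remains as noise. Medians do not add exactly, but the reasoning is the same.

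**How far the groups could differ.** Assume that D is lognormal (log-SD 1.0, truncated at 24 h, the eligibility limit) and that activation is 70% in children arriving within 4.5 h and 50% in later arrivals.
- Median D of 4 h: early share = Φ(ln(4.5/4))/Φ(ln(24/4)) = 0.547/0.963 = 0.57. Early arrivers are then 0.7×0.57/(0.7×0.57 + 0.5×0.43) = 65% of activated children and 0.3×0.57/(0.3×0.57 + 0.5×0.43) = 44% of the others.
- Median D of 1 h: early share = Φ(ln 4.5)/Φ(ln 24) = 0.93. The corresponding shares are 95% and 90%, so there is little left to confound.

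**Simulation.** There are 98 children, medians are compared between action groups, clustering is ignored and the test is two-sided at 5%. In-hospital time H is lognormal. False rejection assumes no true effect and the 70%/50% activation above. Power assumes that half the children receive the action, unrelated to D, and that it cuts H by 33%. All these inputs are assumptions.

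| Median D | Median H (log-SD) | False rejection, last-seen-well clock | Power, last-seen-well clock | Power, arrival clock |
|---|---|---|---|---|
| 4 h | 3 h (0.7) | 23% | 20% | 59% |
| 2 h | 6 h (0.8) | 8% | 33% | 45% |
| 1 h | 6 h (0.8) | 6% | 38% | 44% |

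On the arrival clock, false rejection is about 4–5% throughout. Repeat runs move these entries by up to about 4 points.

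**Sensitivity.** Under the first split:
- The false saving is about 1.7 h.
- With nine hospitals of unequal size (coefficient of variation 0.5) and a clustered standard error, the results are 26% false rejection and power of 21% against 54%. The arrival clock then rejects 7–9% with a normal reference, because there are few clusters, and 4–5% with a t reference on 8 degrees of freedom.
- Weaker dependence (60% versus 50%) gives 12% false rejection in that clustered version.

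**Which split fits the article better.** The first split gives about 19% diagnosed within 4.5 h and the second about 14%; the protocol assumes 15% before implementation. The second and third splits also agree with the Introduction's view that in-hospital delay matters more.

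**The case against.** The strongest reply has four parts.

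1. **The severe scenario makes pre-arrival delay the longer part**, against the Introduction. This stands. With the order reversed, the loss of power is modest and false rejection is close to nominal. A reader might infer that the analysis has little power, or cannot show which actions help; the article gives nothing that establishes either.

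2. **No text ties activation to early arrival.** This also stands. The Interventions and Study procedure sections trigger activation on symptoms, with screening for reperfusion afterwards. The Study setting section lists activation criteria separately from thrombolysis eligibility, and children with symptoms of up to 24 hours are eligible. A reader might infer that bias is expected because treatment is time-limited. It is possible, but the activation rates used above are invented for illustration.

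3. **Interval detail belongs in a fuller plan.** This stands only in part. The method sentence refers to times in the plural, Table 1 holds the components and Figure 4 is not available, so component intervals may be intended. But the article defines the term and then applies it. That is a stated choice, not a gap.

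4. **Last seen well is the right clock for a treatment window, and a later clock has costs.** Both are true. The first supports the clock for the primary outcome, not for the effect of an action taken hours later. The second limits what the fix can achieve.

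Pooling both phases to 196 children would give larger false-rejection figures. It suits PACS activation poorly, because the 2015–2017 cohort was chosen to predate implementation of the protocols.

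**Conclusion.** The point holds as a minor one about a secondary outcome. On the article's only definition, the outcome for EMS and ED actions includes time that those actions could not influence, and no adjustment is named. Precision is lost whenever the earlier delay varies. Bias arises only if the action is related to time since onset, which is not documented.

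Across the assumed scenarios the harm runs from slight (6% false rejection; power 38% against 44%) to severe (23%; 20% against 59%), and the Introduction favours the slight end. The arrival clock did better on power in every scenario and kept its nominal error rate in the unclustered runs. That partly reflects an assumption that in-hospital time is independent of earlier delay.

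Nothing here bears on the primary 4.5-hour outcome, and a reader should not infer that its clock is wrong.

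**What to change.** In the Data analysis plan (Outcomes), name the interval for each action:
- **ED actions** (PACS activation, choice of first imaging): arrival to completion of imaging, adjusted for onset-to-arrival time.
- **EMS actions** (lights/sirens, prenotification): emergency call to completion of imaging, adjusted for onset-to-call time. An arrival clock would miss the part of their effect that falls before arrival.
- **Inpatients**: start from a recorded recognition or Code Stroke time where there is one, or report them separately.
- **Last seen well to imaging**: keep it for the primary outcome, and report it here as descriptive.
- **Interpretation**: describe the results as associations, because confounding by severity or triage priority remains on any clock.

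The cost is a few sentences. Table 1 already collects timelines before and after arrival, and data collection runs to mid-2026, so the intervals can be fixed before analysis. The price is that inpatients without a comparable start time leave the ED-action analysis, and EMS analyses are confined to children who came by ambulance.

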**Figure 4 F4:**
[figure not shown]
PACS study outcome measures and analyses. AIS, arterial ischaemic stroke; AuSCR, Australian Clinical Stroke Registry; BASICS, Brain Attack and Stroke in Children Screen; ED, emergency department; EMS, emergency medical services; PACS, Paediatric Acute Code Stroke; ROC, receiver operating characteristic; tPa, tissue plasminogen activator.

Due to the hospital-based nature of the proposed intervention, when powering this study, we have taken appropriate care of the hierarchical nature of the data, where individual patients are clustered within the treating hospitals. It is therefore appropriate to anticipate the presence of a design effect (expressed through the value of the intraclass correlation coefficient), as would have to be done in the situation of cluster-randomised studies. In addition, different hospitals will be able to recruit different numbers of patients, thus there will be a variation of cluster sizes.

Nine hospitals are participating in the study. At the time of receiving grant funding in July 2020, seven hospitals had agreed to participate in the study. Based on this consideration, assuming the settings of alpha=0.05, the intraclass correlation coefficient of 0.05 (corresponding to a small-to-medium hospital-specific effect) and the coefficient of variation of hospital-based cluster sizes of 0.5 (medium-to-high level of variation) with at least seven hospitals, recruiting the 98 patients with radiologically confirmed diagnosis of stroke in the pre-PACS implementation phase and 98 patients in the post-PACS protocol implementation stage (on average 14 patients per hospital for both pre-implementation and post implementation stages), will yield 80% power to detect a change from 0.15 to 0.40 in proportion of children diagnosed within 4.5 hours of symptom onset.

In addition, this sample size will be sufficient for further validation and continuous updating of the BASICS tool in order to further improve its predictive capacity (as the total number of screened patients is expected to be at least three times the number of confirmed strokes).^30
31^

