Performance accuracy of the BASICS tools will be evaluated (patients dichotomised to diagnosis of stroke or mimic) by ORs, positive/negative likelihood ratios and receiver operating characteristic curves.Interobserver reliability of the BASICS tools will be evaluated using kappa score and confirmed by intraclass correlation coefficient and Lin’s concordance coefficient.Benchmarking primary and secondary outcomes (1) and (2) against adult best practice care through data linkage to the Australian Clinical Stroke Registry (AuSCR)^46^ and ambulance services data. Descriptive statistics will be used to summarise characteristics of children treated in paediatric versus adult hospitals, with differences tested using χ^2^ tests for categorical variables and rank-sum test for non-parametric continuous variables.

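### The tests named for comparing children in paediatric and adult hospitals ignore hospital clustering, so their p-values will tend to be too small

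*Protocol article*

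**What the plan says.** The last item under Outcomes in the Data analysis plan is introduced as "Benchmarking primary and secondary outcomes (1) and (2) against adult best practice care through data linkage" to the Australian adult stroke registry and ambulance data. The next sentence, which opens with descriptive statistics, names the contrast as "characteristics of children treated in paediatric versus adult hospitals, with differences tested using" two methods: χ² where the variable is categorical, and the rank-sum test where it is continuous and non-parametric. No hospital effect, cluster term or adjusted standard error is mentioned, and no other test is given for this item.

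The section on sample size and power takes a different view of the data. It states that "individual patients are clustered within the treating hospitals" and that a design effect should be anticipated. It assumes "the intraclass correlation coefficient of 0.05" and "the coefficient of variation of hospital-based cluster sizes of 0.5", with "on average 14 patients per hospital for both pre-implementation and post implementation stages".

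Earlier in the same Outcomes section, hospital is a random effect in the models for the primary outcome, reperfusion therapy and diagnostic correctness. Hospitals are the clusters in the regression for differences in times.

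**The concern.** The χ² and rank-sum reference distributions assume that each child is an independent draw. Under that assumption, the only null hypothesis they represent is that no hospital differs from any other. The question of interest is whether paediatric and adult hospitals differ on average, which can be false even when individual hospitals vary.

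The omission matters more here than it would in the pre/post analyses. There each hospital contributes to both phases, so stable hospital effects largely cancel. Hospital type never varies within a hospital, so nothing cancels, and the paediatric side has at most nine hospitals. With any positive ICC the unadjusted tests reject a true null too often. A gap that reflects the practice or case mix of a few hospitals would then be more likely than 5% to appear as a significant difference between paediatric and adult care, which is a comparison the Discussion gives weight to.

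**Working it through.** **Inputs from the protocol article.** ICC 0.05, cluster-size coefficient of variation (CV) 0.5, 98 confirmed strokes per phase, 14 per hospital on average in seven hospitals, nine participating hospitals, alpha 0.05 (taken as two-sided), 15% versus 40% diagnosed within 4.5 hours.

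**Assumed, because the article does not give them.** The number of adult hospitals, the number of children in them, and that the ICC of 0.05 carries over to this comparison.

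**Step 1: reproduce the plan's own clustered calculation.**
- Design effect: DE = 1 + [(1 + CV²)m − 1] × ICC = 1 + (1.25 × 14 − 1) × 0.05 = 1.825.
- Unclustered need for 15% versus 40% at 80% power: 49 per phase. 49 × 1.825 = 89.4, or 6.4 hospitals of 14. Rounded up, that is seven hospitals and 98 children.
- Power with 98/1.825 effective children per phase: 79.2% with a t reference on 12 df, and 83.7% by the normal approximation. With no design effect it would be 97.9%.

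The stated 80% is therefore reproduced, and the plan did use a design effect.

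**Step 2: true size of a test that ignores clustering.** For a contrast wholly between hospitals, the true variance exceeds the assumed one by

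V = (DE₁/n₁ + DE₂/n₂) / (1/n₁ + 1/n₂),

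and a nominal two-sided 5% test rejects with probability 2[1 − Φ(1.96/√V)].

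*Comparator hospitals of similar size (ICC 0.05, CV 0.5)*
- 7 versus 7 hospitals of 14: V = 1.825, rate 14.7%. Standard errors are too small by a factor √1.825 = 1.35.
- 98 children in nine paediatric hospitals (mean 10.9, DE = 1 + (1.25 × 10.9 − 1) × 0.05 = 1.63) versus ten adult hospitals of 10 (DE = 1.575): V = 1.60, rate 12.2%.

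*Few children, thinly spread (ICC 0.05, CV 0.5)*
- 98 in nine versus 25 adult hospitals of 2 (DE = 1 + 1.5 × 0.05 = 1.075): V = (1.631/98 + 1.075/50)/(1/98 + 1/50) = 1.26, rate 8.1%.
- 98 in nine versus 30 adult hospitals of 2: V = 1.29, rate 8.4%.
- 98 in nine versus 50 adult hospitals of about 1: V = 1.22, rate 7.6%.

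*ICC 0.02*
- 7 versus 7 of 14: V = 1.33, rate 8.9%.
- 98 in nine versus 25 of 2: V = 1.11, rate 6.2%.

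**Step 3: check by simulation** (beta-binomial data for χ², normal random intercepts for rank-sum, no true difference between hospital types).

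| Configuration | ICC | χ² | Rank-sum |
|---|---|---|---|
| 7 v 7 hospitals of 14, equal sizes | 0.05 | 12.7% | 12.4% |
| 7 v 7 hospitals of 14, CV 0.5 | 0.05 | 14.2% | 13.4% |
| 9 of 22 v 30 of 2, CV 0.5 | 0.05 | 9.2-9.6% | 9.4% |
| 9 of 11 v 50 of about 1, CV 0.5 | 0.05 | 7.8-8.2% | 6.3% |
| 7 v 7 hospitals of 14, CV 0.5 | 0.02 | 9.1% | not run |
| 7 v 7 hospitals of 14, CV 0.5 | 0.01 | 6.7% | not run |

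With an ICC of zero the χ² test holds about 5%, so clustering is the cause of the excess.

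**The case against.** The strongest reply is that the sentence opens with descriptive statistics and concerns characteristics of children, not outcomes. Read literally, the tests belong to a descriptive table, and the preceding sentence about benchmarking outcomes names no test. This stands as a limit on the point: the article does not say outright that the primary outcome will be compared this way. It does not remove the point, because hypothesis tests are specified, they are the only ones given under that item, and a p-value in a descriptive table is equally affected by clustering.

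Second, the ICC is borrowed. It was set for time to diagnosis when powering the pre/post comparison, and no value is given for other variables or for adult hospitals. This also stands, and it is why lower values are shown.

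Third, if the aim were only to describe these particular hospitals as they are, patient-level tests could be defended. The article does not state that narrower aim, and benchmarking against adult best practice suggests a wider one.

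Two stronger readings are tempting. A reader might infer that false-positive rates near 20% are to be expected. Such rates arise if both phases are pooled and the comparator has either hospitals of matching size or thousands of patients. The article does not say that phases are pooled for benchmarking. The sentence concerns children in adult hospitals, and thousands of them is not credible beside 98 confirmed strokes per phase across the paediatric sites. A reader might also infer that ordinary hospital variation will be reported as a difference. The calculation shows only a raised probability of that error.

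**Conclusion.** The point holds as a modest one. The tests fixed for the paediatric versus adult hospital comparison are anti-conservative whenever outcomes or characteristics are correlated within hospital, and they depart from the way the plan handles hospital elsewhere.

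At an ICC of 0.05, a nominal 5% test has a true false-positive rate of roughly 8-10% with few, thinly spread children in adult hospitals, falling slightly lower at about one child per hospital. It is about 12-14% with comparator hospitals of similar size. At an ICC of 0.02 the rate is about 6-9%. The direction follows from the design. The size depends on the assumed adult-hospital numbers and on the borrowed ICC.

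The primary analysis is unaffected, and the plan attaches no power statement or decision rule to this comparison.

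**What to change.** Amend the benchmarking item so that hospital type is a fixed effect in the methods the plan already uses: logistic regression with hospital as a random effect for binary variables, and hospital-clustered quantile regression (the plan's quartile regression) for continuous ones. Use a small-sample reference with degrees of freedom based on the number of hospitals.

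Where adult-hospital clusters are too small to fit these models, or the linked data carry no hospital identifier, present the comparison descriptively without p-values. If an identifier is available, add hospital-clustered confidence intervals. State also whether the tests apply to characteristics only or to the benchmarked outcomes as well.

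The cost is wider intervals, slightly more analysis work and the need to request a hospital identifier in the linkage. No extra patients or study procedures are required.
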